### Measurement and instruments

Outcome variables to be measured are listed in Table 3. Most of the instruments are previously validated and have been used in the same age groups as intended in this study in Norway or other countries.

**Table 3 Tab3:** Description of variables, purpose of measure, instruments, and when data will be collected

Level	Purpose of measure	Variable	Measure	Instrument	When to collect
Infant	SO	Antropo-metric measures	Weight and height	Self-reported, but measured at the scheduled visits to the health centre	At 6 and 12 months (24 and 48 months^a^)
	SO, IC	Food intake Food variance	Daily food intake, breastfeeding, introduction of solid food	FFQ based on FFQ from Norwegian nationwide diet surveys among 6 and 12 months old children [13, 56] and the Norwegian MoBa-study [51]	At 6 and 12 months (24 and 48 months^a^)
	SO, IC	Child eating behaviour	Report of satiety-responsiveness, fussiness, food enjoyment, emotional over−/under eating	BEBQ [57, 58] CEBQ [59, 60] CEBQ	At 6 months At 12 months (24 and 48 months^a^)
	SC	Infant tempera-ment	Infant difficultness as perceived by caregiver	Fussy/difficult subscale of the Infant Characteristics Questionnaire [61, 62]	At 6 and 12 months
	SO, IC	Food preferences	Rating of child’s preferences for listed food and beverages	Food preferences questionnaire developed for this study’s purpose	(At 24 and 48 months^a^)
	SO, SC	Child behaviour	Internalizing and externalizing behaviours	Child Behaviour CheckList (CBCL) [63–65]	(At 24 and 48 months^a^)
Parent	SC	Antropo-metric measures	Weight and height of parent	Self-reported	At 6 and 12 months (24 and 48 months^a^)
	SC	Food intake Food variance	Frequency of intake of indicator foods for healthy and unhealthy food.	FFQ developed for this study’s purpose, based on the Norwegian MoBa-study [51]	At 6 and 12 months (24 and 48 months^a^)
	SO, IC	Food neophobia	Ratings of the parent’s courage to taste new foods and flavours	The food neophobia scale [66]	At 6 months
	SC	Parental eating behaviour	Report of satiety-responsiveness, fussiness, food enjoyment, emotional over−/under eating	Adult Eating Behaviour Questionnaire [67] (AEBQ)	At 12 months (24 and 48 months^a^)
	SO, IC	Feeding style and feeding practices	Feeding attitudes, practices, perceptions/concern regarding weight, under/over-eating, infant cues	Infant Feeding Questionnaire [68, 69] Child Feeding Questionnaire [70]	At 6 and 12 months (24 and 48 months^a^)
	SO, IC	Feeding self efficacy	Parental self- efficacy in feeding situations	Five items from the Feeding Self-Efficacy Questionnaire [71, 72]	At 6 and 12 months (24 and 48 months^a^)
	SO, IC	Parenting style	Parental discipline, routine, anxiety, nurturance and involvement	Infancy Parenting Styles Questionnaire [73]	At 6 and 12 months
	SO, IC	Parenting style	Control-oriented parenting	The Parental Locus of Control Scale (PLOC), short version [74, 75]	At 12 months (24 and 48 months^a^)
	SC	Parental personality traits and mental health	General self-efficacy Negative Affectivity	Short versions of: General Self-Efficacy Scale (GSE) [76, 77] The (Hopkins) Symptoms Checklist (SCL-8) [76, 78, 79] Edinburgh Postnatal Depression Scale (EPDS) [80, 81]	At 6 and 12 months (24 and 48 months^a^) At 12 months

*SO* Study outcome, *IC* Intervention component, *SC* Study covariate, *FFQ* Food frequency questionnaire, *BEBQ* Baby Eating Behaviour Questionnaire, *CEBQ* Child Eating Behaviour Questionnaire

^a^Possible follow-up studies, not yet planned

### User involvement and process-evaluation

As a prelude to the development of the intervention, a group of public child health nurses in a municipality were interviewed regarding their perceptions and experiences with nutritional guidance to parents of infants and toddlers. Since Norwegian children are followed regularly by the municipal health centers, the public child health nurses are important stakeholders when it comes to advice and guidance on infant nutrition. The public child health nurses also constitute a significant user group. Their perception of an intervention’s usability is crucial to whether they recommend it to their parents. The public child health nurses provided valuable key insights that were used in the development of the intervention.

After developing the script for the intervention’s theme-films, a group of seven parents gave feedback on the scripts’ content in terms of how well it matched their child’s age, if the text was easily understood and if the content was perceived as important and relevant.

To evaluate the intervention, we have also included questions for parents in the intervention group about their experiences in the questionnaire at T2 (12 months). In addition, a Master student has conducted qualitative in-depth interviews with seven parents in the intervention group about their expectations and the perceived usefulness of the intervention.

### Sample size calculations

Daniels et al. in the NOURISH study protocol [7] estimated that 265 participants per group would be a sufficient sample size to be able to detect differences in feeding practices with 80% power and type error I of 5%. Their observed differences in weight measures did not, however, reach statistical significance [17]. Taking this into account, we estimated that we needed 400 participants in both control and intervention arm (800 in total) and aimed to recruit 500 in each group assuming a completion rate of 80%.

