**Methods:**

During springtime 2016, parents of children aged between 3 and 5 months were recruited through Norwegian child health centres and announcements on Facebook. After completing the baseline questionnaire, 718 parents were individually randomized to intervention- or control group. The intervention group received monthly emails with links to an age-appropriate web-site when their child was between 6 and 12 months. The control group received ordinary care from the child health centres.

The data-collection is ongoing. All participants will be followed up at ages 12 and possibly 24 and 48 months, with questionnaires relating to eating behaviour and feeding practices, food variety and diet quality.

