### Recruitment and participants

We used two parallel recruitment strategies in this study:

An email was sent to all the municipality child health centres in Norway. This email contained a link to a customized information-website for the municipality’s child-health services. The website included an article about the study published in the Norwegian journal for public child health nurses [45] and a short promotional film in addition to printable posters and parent-leaflets. Nurses could, if they found it appropriate, inform their parents about the possibility of participating in this study. Parents who were interested could give their informed consent and enrol themselves on the study’s homepage [46] if their children met the inclusion criteria.

Recruitment was also done through announcement on Facebook. An advertisement with a short film presented the study. Parents wishing to participate could give their informed consent and enrol themselves on the study’s homepage if their children met the inclusion criteria.

The recruitment lasted 3 months, from March to June 2016. During this period 1010 participants enrolled themselves on the study’s homepage, but 50 of the participants registered themselves more than once. Of the remaining 960 participants, 718 parents completed the baseline questionnaire. Of these, the majority were recruited through Facebook (Table 1). Among the participants, there was a very high percentage of mothers compared to fathers, and the group as a whole had a relatively high educational level. The geographical distribution of participants reflected the geographical population density in Norway, except for a slightly higher proportion of participants from the southern parts of Norway and somewhat lower from the eastern parts of Norway.

**Table 1 Tab1:** Characteristics of the participating parents (*n* = 718)

Characteristics			Value^a^
Recruitment strategy			
		Recruited through Facebook	89,8
		Recruited through child health centers	2,1
		Recruited through both Facebook and child Health centers	2,2
		Other (parents/friends/media)	5,8
Parents			
	Mothers/Fathers		99,6/0,4
	Age (years)		30.5 (4.4)
	Education		
		Upper secondary school or less	19,1
		College/university ( ≤ 4 years)	36.9
		College/university ( ≥ 4 years)	43.9
	Geographic residence		
		Northern parts of Norway	7,5
		Middle parts of Norway	8,5
		Western parts of Norway	29,6
		Southern parts of Norway	14,2
		Eastern parts of Norway (included capital)	40,2

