## Discussion

The completion rate at baseline was 75%, slightly lower than what we assumed. Parents who wanted to participate in the study could be enrolled when the child was 3 months old, but the questionnaire prior to randomization and intervention were to be submitted when the child was between five and 6 months old. The time span between study recruitment and the baseline questionnaire may explain the drop-offs of participants from recruitment time to inclusion and randomization.

Although both mothers and fathers were invited to participate in the study, a large majority of the recruited participants were mothers. It may be that more mothers than fathers are frequent users of Facebook, and that this way of recruitment is not as suitable for men as for women. However, according to Plantin & Daneback, parent’s online behaviour reflects their offline behaviour when it comes to searching for information about health and parenting at the Internet. That mothers more frequently than fathers are searching for health-related information on the web, may reflect that women most often take the main responsibility for the hands-on healthcare of the family [23, 49]. This corresponds with other research in this area, which until now has been dominated by research on mothers and children [31].

The educational level in the participant group was relatively high, which may raise questions about selection bias and limited generalizability of results. This skewness is well known from epidemiological research. Lower participation and response rates in groups from less advantaged socio-economic classes have been a major concern in many population-based health surveys [50]. This is also seen in the large Norwegian Mother and Child cohort study (MoBa) [51], where the participating mothers had healthier lifestyle patterns and higher socio-economic status than the average population [52, 53]. Two studies comparing MoBa participant’s data with non-participant’s data obtained from national registry-data, found that differences between the groups had implications for prevalence studies but did not appear to compromise exposure-outcome associations [53, 54].

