## Conclusion

The early living environment is important for children’s development and may lay the foundation for lifelong patterns. This also applies to the establishment of early eating habits. Providing parents with guidance on diet and nutrition during this significant period is an important task for the health authorities and public child health services. Parents, especially mothers, are extensive users of the Internet to seek for health-related information regarding their children. Despite this, there are few randomized controlled studies investigating the use of Internet to promote healthy eating habits in early childhood, which may prevent childhood overweight and obesity and lay a good foundation for future health.

The eHealth intervention in *Early Food for Future Health* guides parents of children between 6 and 12 months of age through food-related developmental stages in the weaning period. It is an intervention with focus on promoting early healthy food-habits suitable for all children and parents. The size of the study, the web-based design and the comprehensive mapping of possible modifying factors may provide greater insight and understanding of the important field of preventing childhood overweight and obesity on following topics: Design and efficacy of internet-based interventions and the complex and reciprocal relationship between parenting, feeding behavior and children’s eating behavior.

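### Recruitment closed with 718 parents randomised against a stated need of 800, and the article's completion allowance is compared with losses before randomisation, so 400 per arm cannot be reached at 12 months

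*Protocol article*

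**What the plan says.** Under Sample size calculations, the article takes as its reference an earlier Australian feeding trial whose protocol set 265 per group for differences in feeding practices, at 80% power and 5% type I error. It notes that the weight differences in that trial were not significant. Taking this into account, it says "we estimated that we needed 400 participants in both control and intervention arm (800 in total) and aimed to recruit 500 in each group", with an assumed completion rate of 80%. It gives no outcome, effect size, standard deviation or power for the 400.

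The numbers obtained are in the Abstract and under Recruitment and participants. There were 1010 registrations, "but 50 of the participants registered themselves more than once", and then: "Of the remaining 960 participants, 718 parents completed the baseline questionnaire". The Abstract says "718 parents were individually randomized to intervention- or control group". Study design places randomisation at completion of the baseline questionnaire and says that recruitment ended in June 2016. Follow-up is at 12 months of age; 24 and 48 months are only possible.

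The Discussion says "The completion rate at baseline was 75%, slightly lower than what we assumed", and places these losses between recruitment and randomisation. The Conclusion begins its list of the study's contributions with "The size of the study, the web-based design and the comprehensive mapping of possible modifying factors".

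**The concern.** Two things do not fit together. First, the stated need is 800 and the number randomised is 718. Recruitment is closed, so 718 is a ceiling, yet the article never sets the two figures side by side.

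Second, the completion allowance appears in two roles. In the sample size section, 500 per arm at 80% gives 400 per arm, which reads most naturally as an allowance for loss up to the point of analysis. The Discussion compares the assumed rate with completion of a questionnaire that comes before randomisation. Used that way, the allowance covers self-enrolled parents who never entered the trial, and nothing is set aside for randomised parents who do not return the 12-month questionnaire. Only the latter loss reduces the number analysed.

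At stake is an accurate statement of the trial's precision, made before the data are analysed. The need was raised from 265 to 400 per arm because of the weight measures, and child BMI and weight are the secondary outcomes. A null result there should be read against the number the trial can have, not against 400 per arm.

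**Working it through.** **Inputs.** Need of 400 per arm, target of 500 per arm, 80% completion, and 265 per group at 80% power and 5% error in the earlier trial (Sample size calculations); 1010 registrations, 50 duplicates, 960 unique enrolees, 718 completing baseline (Recruitment and participants); 718 randomised (Abstract). Assumptions not in the text: an equal split between arms (arm sizes are not given, and the flowchart was not visible in the copy reviewed), and retention after randomisation.

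**1. The plan's own figures reproduce.**
- Target: 400 / 0.80 = 500 per arm, 1000 in total.
- Unique enrolees: 1010 − 50 = 960.
- Baseline completion: 718 / 960 = 74.8%, stated as 75%.

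**2. Number randomised against the need.**
- 800 − 718 = 82; 82 / 800 = 10.25%.
- 718 / 2 = 359 per arm if split equally. Under any split, at least one arm is below 400.
- Retention needed for 800: 800 / 718 = 111%, which is impossible.

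This holds on either reading of completion. If the 400 means parents with 12-month data, 718 randomised cannot supply 800. If it means parents who completed baseline, 718 is still below 800, and no allowance for later loss has been stated.

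**3. Expected number analysed per arm at 12 months: 718 × retention / 2.**

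| Assumed retention | Total | Per arm |
|---|---|---|
| 95% | 682 | 341 |
| 90% | 646 | 323 |
| 80% | 574 | 287 |
| 75% | 538 | 269 |
| 70% | 503 | 251 |

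**4. Illustrative detectable difference.** Two-sided 5% test, 80% power, continuous outcome, equal arms, no baseline adjustment: d = (1.960 + 0.842) × √(2/n), in SD units.
- n = 400: 0.198
- n = 359: 0.209
- n = 287: 0.234

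If the 400 had been chosen for 80% power, which the article does not say, power for 0.198 SD would be Φ(0.198 × √(n/2) − 1.960): 75.6% at 359 and 66.0% at 287 per arm.

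**5. The one size tied to a power statement.** By the same formula, 265 per group corresponds to 0.243 SD.
- Power for 0.243 SD: 90.3% at 359 and 83.0% at 287 per arm.
- Retention at which 265 per arm is just met: 530 / 718 = 73.8%.

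**The case against.** The strongest reply is that nothing is miscalculated or hidden. The 400 and 500 are prospective targets given in the past tense, the 718 is reported openly in several places, and no sentence claims that 400 per arm was achieved. The remark in the Discussion is literally correct: 75% is a little below 80%. All of this stands. The fault is that the rate is compared at the wrong stage, and that the shortfall against 800 goes unmentioned.

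A reader might infer from the Conclusion that the authors present the size as being what was planned. The text does not support that. It lists size, with the web-based design and the mapping of modifying factors, among features that may add insight, and says nothing about the target.

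A reader might also infer that the trial is underpowered for its primary outcomes. The documents do not show this either. The 80% power belongs to the earlier trial's 265 per group, not to the 400, so any power figure for 400 per arm rests on an added premise. The article also plans multivariate analyses and has baseline measures for most primary outcomes. If baseline adjustment were used, a baseline–outcome correlation of about 0.53 would make 287 per arm equivalent to 400 unadjusted (1 − 0.53² ≈ 287/400 = 0.72). That correlation is an assumption, not a figure from the article.

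Finally, the 75% seen before randomisation is no forecast of later retention. It describes self-enrolees who had not yet completed anything, whereas the randomised parents had all completed baseline. Retention must therefore be shown as a range that includes high values.

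A condensed article may leave much to a full protocol. That does not answer this point, because the need, the target, the rate and the number randomised are all stated here and do not agree.

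**Conclusion.** The point holds, at the level of should-fix. The stated need of 800 cannot be met by 718 randomised at any retention, and the article's only completion allowance is compared with a loss that occurred before randomisation. The size is 82 participants (10.25%) before follow-up loss. After follow-up loss it is about 251 to 341 per arm for assumed retention of 70% to 95%, with 287 at 80%. These per-arm figures assume an equal split.

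The consequence is limited. The feeding-practice reference of 265 per group is still met at retention of about 74% or more, so what is mainly lost is part of the margin from 265 to 400 that was added because of the weight measures. The shift in detectable difference from 0.198 to 0.209 or 0.234 SD is illustrative only, because the article fixes no effect size or power for 400 per arm. The documents do not support a conclusion that the primary comparisons fail, or that the shortfall was concealed.

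**What to change.** Change the wording; no further enrolment and no change of design or analysis is needed.

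1. In Sample size calculations, state that the target of 800 was not reached and that 718 were randomised, with the actual arm sizes.
2. In the Discussion, report completion before randomisation (718/960 = 75%) separately from retention after randomisation, and say to which of the two the assumed 80% was meant to apply.
3. Give the expected number analysed at 12 months over a range of retention labelled as assumed, for example 70% to 95% (about 251 to 341 per arm; 287 at 80%).
4. If a detectable difference is quoted, name the outcome and the assumptions, and mark it as illustrative.
5. State that the 265-per-group reference for feeding practices is met if retention is about 74% or more, and that the shortfall bears mainly on the margin added because of the weight measures.

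The cost is a few sentences and a less favourable statement of precision. The article says the data have not been analysed, so this can be put on record before results are known.

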### Data analyses

Data have not yet been analysed. To detect potential differences in study outcomes between the intervention and control groups, between-group comparisons and multivariate analyses will be done.

## Discussion

The completion rate at baseline was 75%, slightly lower than what we assumed. Parents who wanted to participate in the study could be enrolled when the child was 3 months old, but the questionnaire prior to randomization and intervention were to be submitted when the child was between five and 6 months old. The time span between study recruitment and the baseline questionnaire may explain the drop-offs of participants from recruitment time to inclusion and randomization.

Although both mothers and fathers were invited to participate in the study, a large majority of the recruited participants were mothers. It may be that more mothers than fathers are frequent users of Facebook, and that this way of recruitment is not as suitable for men as for women. However, according to Plantin & Daneback, parent’s online behaviour reflects their offline behaviour when it comes to searching for information about health and parenting at the Internet. That mothers more frequently than fathers are searching for health-related information on the web, may reflect that women most often take the main responsibility for the hands-on healthcare of the family [23, 49]. This corresponds with other research in this area, which until now has been dominated by research on mothers and children [31].

The educational level in the participant group was relatively high, which may raise questions about selection bias and limited generalizability of results. This skewness is well known from epidemiological research. Lower participation and response rates in groups from less advantaged socio-economic classes have been a major concern in many population-based health surveys [50]. This is also seen in the large Norwegian Mother and Child cohort study (MoBa) [51], where the participating mothers had healthier lifestyle patterns and higher socio-economic status than the average population [52, 53]. Two studies comparing MoBa participant’s data with non-participant’s data obtained from national registry-data, found that differences between the groups had implications for prevalence studies but did not appear to compromise exposure-outcome associations [53, 54].

In this study, we anticipated that using advertising on Facebook as recruitment method and an easy accessible, online study design would make it easier for parents from lower socioeconomic levels to participate. This does not seem to be the case, and raises the question if use of Internet-based strategies could be even more prone to selection bias. Few studies have investigated this, but a recent Danish study evaluated the occurrence of selection bias in an Internet-based study of pregnancy planners using external data from the Danish Medical Birth Registry. They found that recruiting reproductive aged women through the Internet did not led to more selection bias than traditional methods of recruitment [55].

